## Abstract

**Background:**

Juvenile antisocial behavior can have long-lasting and devastating effects for juveniles themselves, victims, and society. Evidence-based treatment is vital. Forensic Outpatient Systemic Therapy (Forensische Ambulante Systeem Therapie; FAST) is a promising treatment for juveniles showing severe antisocial behavior including aggression, (domestic) violence, and delinquent behavior. FAST has a flexible intensity and length, addresses individual and systemic risk and protective factors, and is responsive to the abilities of the client (system), intervention characteristics all considered crucial for effective treatment. The current study will investigate whether FAST is effective in reducing aggression of the juvenile, reaching client formulated subgoals, and improving family functioning. Processes of change will be examined, as well as mediation by reaching client formulated subgoals and improved family functioning.

**Methods:**

A Multiple Case Experimental Design (MCED) with an ABC design will be performed (A = baseline, B = intervention, and C = follow-up). Juveniles with primary aggression and/or anger problems (*N* = 15) and their caregiver(s) will be recruited. Data collection will consist of self-report questionnaires and case file analysis. Participants fill out frequent short self-report questionnaires (twice a week during phase A, every other week during phase B, and every week during phase C) and two main questionnaires at the start of the intervention and immediately after intervention end, thereby covering a period of 5 to 11 months. Both visual and statistical analyses will be performed.

**Discussion:**

This study will generate robust knowledge and inform clinical practice on the effectiveness, processes of change, and mediating mechanisms of FAST, aiming to improve the treatment of future families within youth forensic care.

**Trial registration:**

This trial was registered at ClinicalTrials.gov on 28/08/2023, protocol ID 60-63600-98-1138a.

## Introduction

Juvenile antisocial behavior, including aggression, (domestic) violence, and delinquent behavior such as threatening, assault, property crime, and substance and weapon offences [1], can have long-lasting and devastating effects for victims [2, 3] and perpetrators. Victims experience long-lasting damaging consequences such as feelings of unsafety [4] and are at increased risk of developing social emotional problems [5, 6]. Juveniles exhibiting antisocial behavior have a heightened risk of out of home placement, delinquency, and recidivism [7]. They are less likely to have stable living situations, work environments, and relationships [8], induce high societal costs, and negatively affect societal safety [9]. Considering the long-lasting personal and societal consequences of juvenile antisocial behavior [8–10], evidence-based treatment is vital for not only the juveniles and their systems but also for society. Although various intervention programs are available for this target group, these programs generally do not achieve substantial and long-lasting effects in the reduction of antisocial behavior and recidivism [11, 12].

Forensic Outpatient Systemic Therapy (in Dutch: Forensische Ambulante Systeem Therapie; FAST) is an outpatient systemic intervention for juveniles (aged 12–21 years) who show antisocial behavior and their families, developed to (1) reduce juvenile antisocial and/or delinquent behavior; (2) prevent out of home placement; and (3) prevent or decrease recidivism (risk) [13]. Based on Bronfenbrenner’s socio-ecological theory [14], FAST aims to reach intervention goals by targeting juvenile, family, and systemic factors associated with the development and continuation of antisocial behavior, using components that originate from system therapy, cognitive behavioral therapy, aggression regulation therapy, and non-violent resistance.

In addition, FAST aims to be very adherent to the Risk Needs Responsivity (RNR) principles [15]. The RNR model states that, to be effective, interventions should adhere to several principles, among which the RNR are most important: (1) the risk principle: the intensity of the treatment should be adjusted to the recidivism risk; (2) the needs principle: the treatment should target the dynamic individual criminogenic needs; and (3) the (specific) responsivity principle: the treatment needs to be responsive to the abilities of the client (system) and needs to apply interventions that are effective in the target group. FAST has a flexible intensity and length, addresses risk and protective factors within the broad social context of a client system, and is responsive to the abilities of the client (system). In addition, if needed, FAST can be combined with other interventions to address specific individual risk factors of the client (system).

Previous pre-posttest studies showed that FAST resulted in positive changes on the desired outcomes: FAST had a large effect in reducing general recidivism risk, a moderate effect in decreasing problems in the emotional/personal functioning of the juvenile, and a small to moderate effect in improving family functioning [16]. However, more robust studies are needed to be able to attribute these results to the program offered. In addition, processes of change and the theorized mediators, i.e., whether changes in dynamic risk and protective factors result in decreased antisocial behavior, have not yet been investigated.

### Intervention subgoals

Based on both the RNR model [15] and the socio-ecological model [14], FAST subgoals have been formulated based on the dynamic risk and protective factors at the level of the individual, family, and the broader system of the juvenile to reach intervention goals. At the individual level, FAST aims to target juvenile criminogenic risk factors related to psychological functioning such as cognitive distortions [17–19] and low executive functions such as cognitive flexibility, inhibition [20, 21] and coping skills [22, 23]. In addition, FAST aims to effectuate adequate daytime activities [18, 24]. At the family level, FAST aims to improve family functioning, by increasing caregiver-juvenile relationship quality [25, 26] and caregiver behavior [27], and by decreasing caregiver-juvenile conflict [28]. At the level of the broader system, FAST aims to promote social support [29, 30], reduce interaction with deviant peers [31, 32], and decrease truancy [33].

### Aims of the study

The current protocol paper describes a Multiple Case Experimental Design (MCED) study investigating the effectiveness of FAST. The aim of the MCED is to investigate the effectiveness of FAST in reaching its primary intervention goal, i.e., reducing aggression, in reaching client formulated subgoals, and in improving family functioning (i.e., reducing juvenile-caregiver conflict and increasing caregiver responsiveness). In addition, the aim is to investigate processes of change within FAST, i.e., the onset, variability, trend, slope, and sequence of change [34] of the intervention (sub)goals. Further, the aim is to investigate whether reaching client formulated subgoals and improving family functioning indeed function as mediators in the effectiveness of FAST, i.e., whether they contribute to decreases in aggression [13].

Client formulated subgoals measure to what extent the FAST subgoals clients want to achieve during intervention are achieved. In addition, for all families, the FAST subgoal of improving family functioning will be investigated, by examining juvenile-caregiver conflict and caregiver responsiveness [13]. Both constructs have been shown to be crucial in achieving change in family functioning, and proposedly result in a decrease of aggression. Patterson [35] proposed that caregiver-juvenile conflict involves coercive interaction cycles that lead to the development of juvenile conduct problems. Indeed, longitudinal studies have shown caregiver-juvenile conflict to predict juvenile antisocial behavior [36] and aggression [37]. In addition, multiple (meta-analytic) reviews have shown that lower caregiver responsiveness (i.e., feeling insufficiently equipped in parenting skills) is associated with increased externalizing behavior of juveniles [38, 39], especially for samples of older children [38].

The hypotheses are that (1) FAST is effective in reducing aggression; (2) FAST is effective in reaching client formulated subgoals; (3) FAST is effective in improving family functioning (i.e., decreasing juvenile-caregiver conflict and increasing caregiver responsiveness); and (4) improvements in client formulated subgoals and family functioning mediate FAST effectiveness.

In addition to (quasi) experimental studies, MCEDs are increasingly used to study intervention effectiveness in youth populations [40]. The current study is part of a larger research project to determine the effectiveness of FAST and compliments a randomized controlled trial (RCT) [41] because of several design-specific benefits. First, MCEDs can capture within-person changes and intervention effects [40] that might not be detected using group-level analyses [42, 43]. Individual variability in response to treatment seems overlooked in group-level studies on youth interventions [44], highlighting the importance of combining group-level studies with MCEDs. Second, MCEDs allow a precise study of processes of change [45]. The multiple assessment points of an MCED allow detailed documentation [46] to examine the onset, variability, trend, and slope of change and the sequence of changes across different constructs [34]. In addition, the frequent measurements allow monitoring of micro-processes, whilst increasing ecological validity by reducing recall bias [47, 48]. Thereby, MCEDs allow the identification of small behavioral or mental changes. Third, the multiple measurements within each phase of the MCED design allow for a relatively small sample size [45]. Fourth, the design allows to assess if the intervention effect and mediating mechanisms vary between participants, and therefore to what extent effects and mechanisms can be generalized to other cases [44]. Previous MCED intervention studies have found individual differences in the processes of change [49–51], substantiating the importance of utilizing this design in intervention research.

## Methods

### Design

An ABC design will be used with at least five assessment points per phase [45]. Phase A (baseline) covers the first 3–5 weeks of FAST during which the preconditions to enter treatment are created. For all families this part involves a focus on risk management, and for some families it involves a focus on exploratory diagnostics. Phase B covers the subsequent period of 2–8 months, starting with preliminary treatment that is replaced by customized treatment once the treatment plan has been finalized. Phase C (follow-up) covers six weeks after intervention end. The study has a multi-informant (juveniles and caregivers) design. Participants complete short questionnaires during phases A, B, and C with varying frequency: twice a week during phase A, every other week during phase B, and every week during phase C. Additionally, participants fill out two more elaborate questionnaires at the start of FAST and after finishing FAST, and case-file analysis is conducted. The study was registered at ClinicalTrials.gov on 28/08/2023 (protocol ID 60-63600-98-1138a). See Fig 1 for the SPIRIT schedule of enrollment, interventions, and assessments, Fig 2 for a conceptual model of the study design, and S1 Checklist for the SPIRIT checklist.

**Fig 1 pone.0298057.g001:**
[figure not shown]
SPIRIT schedule of enrollment, interventions, and assessments.

**Fig 2 pone.0298057.g002:**
[figure not shown]
Conceptual model of study design.

### Setting

FAST is offered by de Waag, an outpatient forensic mental health care center in the Netherlands with 12 treatment sites. Clients are referred by the juvenile justice system or voluntarily by mental healthcare professionals, school care coordinators, and general practitioners. FAST therapist teams at seven treatment locations will approach participants for the study. Participant recruitment started on September 26^th^ 2023. Participants will be recruited until August 2024. The expected complete date range for participant recruitment and follow-up is September 26^th^ 2023 to July 2025.

### Participants

It is currently unknown how many case series should be included in an MCED study to provide evidence of intervention effectiveness [52]. Numbers range from 3 [53] to 9 [54] or 10 case series [55]. Therefore, complete data will be collected for at least *N* = 10 families. Taking drop-out of treatment and/or the study into account, *N* = 15 juveniles and their caregiver(s) will be recruited. The target group of FAST is diverse in terms of (comorbid) problems, but approximately 93% of the referred juveniles has a behavioral disorder [13] and they often grow up in families with multiple and complex problems. In FAST, 75% of juveniles is male.

#### Inclusion and exclusion criteria

FAST therapists assess whether clients meet the inclusion and exclusion criteria of FAST during the standard intake procedure of FAST. The FAST inclusion criteria are: (1) Juvenile has an estimated IQ-score of 80 or higher and/or sufficient adaptive skills to benefit from FAST; (2) Juvenile is aged 12 to 21 years old at the start of the intervention; (3) Juvenile exhibits externalizing behavior resulting in problems in at least two life areas (family, school, or leisure time), determined by clinical impressions based on information from intake and/or referrer information; (4) Juvenile has a medium to high recidivism risk, measured by the Risk Assessment Instrument for Outpatient Forensic Mental Health Care Youth (RAF GGZ Youth) [56]; (5) Presence of juvenile-caregiver relationship problems, measured by the RAF GGZ Youth; (6) Juvenile has a diagnosis of a DSM-5 behavioral disorder, which is determined using a new diagnostic process or case file analysis; (7) Juvenile and caregiver(s) cannot be motivated to follow treatment at the treatment site after multiple attempts by the therapist; and (8) Juvenile resides with their caregiver(s) or is expected to return to residing with their caregiver(s) within the first two months of FAST. The FAST exclusion criteria are: (1) Juvenile exhibits severe psychiatric symptoms requiring admission; (2) Problem behavior of the juvenile is caused primarily by substance abuse problems, and it is expected that treatment of the substance abuse problems will decrease the problem behavior; and (3) The safety of the family members or therapist cannot be sufficiently guaranteed.

To be eligible for participation in this specific study, one modified study inclusion criterium applies, i.e., the juvenile has primary aggression and/or anger problems (approximately 80% of referred juveniles). Thereby, juveniles exhibiting primarily sexually transgressive behavior, truancy, or property crimes are excluded from the study. In addition, one study exclusion criterium applies, i.e., the juvenile is in secure residential care or confined in a correctional or detention facility at the start of the intervention.

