### Procedure

During intake, therapists evaluate whether clients meet the eligibility criteria and ask juveniles and/or caregiver(s) permission to share their contact details with the researcher. If they agree, FAST clients will be approached by the main researcher or research assistants, whom all have signed a non-disclosure agreement and provided a certificate of conduct, and receive verbal and written information about the study. The researcher obtains written informed consent from juveniles and caregivers for own participation, and from caregiver(s)/legal representative(s) for juveniles younger than 16 years.

During the study, participants fill out short questionnaires that contain approximately 37 items, taking about six minutes [57]. In addition, participants (juveniles and caregivers) complete two more elaborate questionnaires (30 minutes): prior to, or during the first weeks of intervention (pre-test; T1) and immediately after intervention (post-test; T2). These data are used for more extensive assessment at the start and end of the intervention and to assess background information of participants. Therapists fill out two questionnaires (5 minutes) at T1 and T2, providing background information on therapist characteristics. Further, case file analysis will be used to retrieve information on the primary diagnosis of the juveniles, out of home placement, and questionnaires that are filled out as part of the standard FAST procedure by juveniles, caregivers, and therapists.

Given the complexity of the problems the target group faces, which often adversely affects their motivation to participate in treatment or research, the data collection is adjusted to the preferences and agenda of the participants for timing and location (e.g., by (video) phone calls or at the homes of the families). Trained research assistants are available to assist with filling out the questionnaires, e.g., by taking them in interview form. Participants receive financial compensation for filling out the questionnaires: 2.50 euros per short questionnaire and 15 euros per elaborate questionnaire. When completing all measurements, participants receive an average total of 95 euros.

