### Family functioning

Juvenile-caregiver conflict will be measured using the adolescent and parent versions of the Network of Relationship Inventory (NRI) [63], containing six items. An example item is “How much do you and your parents disagree or argue with each other?” for juveniles and “How much do you and your child disagree or argue with each other?” for caregivers. Caregiver responsiveness will be measured using the Nijmeegse Parenting Questionnaire (NPQ) [64], containing eight items. An example item is “If I’m sad or worried about something, my caregiver notices” for juveniles and “If my child is sad or worried about something, I notice it” for caregivers.

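### Entry criterion 8 and a 3–5 week baseline let a change of residence fall between or near the phases, so the A–B change in conflict and caregiver-rated aggression can mix treatment with contact

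*Protocol article*

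**What the plan says.** In the protocol article, the section on inclusion and exclusion criteria gives FAST criterion 8: "Juvenile resides with their caregiver(s) or is expected to return to residing with their caregiver(s) within the first two months of FAST". The only study-specific exclusion that concerns living situation applies when "the juvenile is in secure residential care or confined in a correctional or detention facility at the start of the intervention". A juvenile in another out-of-home setting who is expected back in time stays eligible.

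The Design section states that "Phase A (baseline) covers the first 3–5 weeks of FAST" and that "Phase B covers the subsequent period of 2–8 months". Phase C is the six weeks after the intervention ends. Short questionnaires are completed "twice a week during phase A, every other week during phase B, and every week during phase C".

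Table 1 and the Measures sections list what these questionnaires contain: aggression (YSR from the juvenile, CBCL from the caregiver), conflict (NRI) and responsiveness (NPQ) from both informants, and the prioritised goals. Conflict is asked of caregivers as "How much do you and your child disagree or argue with each other", and responsiveness with items such as "If my child is sad or worried about something, I notice it". The Procedure section adds that "case file analysis will be used to retrieve information on the primary diagnosis of the juveniles, out of home placement".

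The plan of data analysis compares levels and slopes between phases, separately for each variable and each participant. Living situation is not mentioned there. The Introduction names prevention of out-of-home placement as one of the three aims of FAST.

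**The concern.** Each case serves as its own control, so the comparison of phase A with later phases is informative only if the conditions of reporting stay alike apart from treatment. How often a caregiver and a juvenile argue, and how much aggression the caregiver sees, plausibly depend on whether they live under one roof. If a juvenile is away throughout the baseline and at home for most of phase B, the opportunity for conflict rises at about the time treatment starts. A real reduction in at-home conflict could then appear as no change or as worsening.

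A second route leads to the same confounder but does not come from criterion 8. A juvenile who was at home at entry may be placed elsewhere during phase B or C. Conflict and caregiver-observed aggression could then fall because contact has fallen, although FAST counts the placement itself as an unfavourable result.

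In neither case can the questionnaire series alone show what happened, because no item described for it records where the juvenile is living.

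**Working it through.** **Timeline, from the article's own figures** (1 month = 365.25/12/7 = 4.35 weeks)

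- Return window: 2 × 4.35 = 8.7 weeks from the start of FAST.
- Phase A: 3 weeks × 2 = 6 measurements, up to 5 weeks × 2 = 10. All lie inside the return window.
- Part of the window that falls in phase B: 8.7 − 5 = 3.7 weeks, up to 8.7 − 3 = 5.7 weeks. At one measurement per two weeks this is 1.85 to 2.85, or about 2–3 measurements.
- Shortest phase B: 2 months = 8.7 weeks, or 8.7/2 = about 4 measurements. Longest: 8 months = 34.8 weeks, or about 17.

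The most exposed case therefore has a wholly out-of-home baseline and a phase B that is partly or mostly at home.

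**Is residence already among the items?** The article puts the short questionnaire at approximately 37 items. The listed content adds up to that: 19 (aggression) + 6 (conflict) + 8 (responsiveness) + 3 (goals) + 1 (change of goals) = 37. The extra items on criminogenic needs are conditional and concern truancy, substance use, deviant peers and delinquency. No residence item is described.

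**Weight of one case.** 1/15 = 6.7% of recruited families; 1/10 = 10% of the minimum with complete data.

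**Possible size, as an illustration.** The documents give no standard deviation and no home-versus-away difference, so both are assumed. Let d be the rise in conflict at home compared with away, in within-person SD, over the range 0.5, 1 and 2. Take 8 measurements in A and 11 in B (about 4 weeks and 5 months).

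- Away in A, home from the third B measurement, no treatment effect: mean change = d × 9/11 = +0.41, +0.82, +1.64 SD, a spurious worsening. If FAST lowers conflict by δ throughout B, the observed change is −δ + 9d/11. With d = 1, a true benefit of 0.82 SD would show as zero.
- Home in A, placed away after the third of 11 B measurements, no treatment effect: mean change = −d × 8/11 = −0.36, −0.73, −1.45 SD, a spurious improvement in level.
- Whether the second pattern would pass the plan's clinical-relevance cut (Percentage of Non-overlapping Data above 80%) was simulated with 20,000 series per setting and lag-one autocorrelation of 0 or 0.3. It passed in 0.4–1.5%, 1.7–3.7% and 9.9–13.7% of series for d = 0.5, 1 and 2. With placement at the very start of B the figures were 0.7–2.3%, 5.2–9.2% and 43.5–49.2%. With no shift at all they were 0.1–0.3%.

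The shift in mean level follows directly from d. Passing the 80% cut needs a large and early shift.

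**The case against.** The strongest reply has four parts.

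- **The data exist and the handling may be planned elsewhere.** Placement is read from case files, and a condensed article need not state how such events are analysed. This stands: the missing analysis rule is not itself the fault. The fault is that the entry criterion and the phase lengths, both fixed in the article, interact badly. A later rule can separate residence from treatment only if residence is dated against each measurement. Whether the case files allow that is unknown.
- **The A–B level contrast is not the whole evidence.** There is also visual analysis, slope change, phase C and juvenile self-report of aggression. This stands in part. A plotted case may show an abrupt step, and self-report is less clearly affected. Phase C does not repair an away baseline, because an A–C comparison uses the same baseline.
- **Direction.** A reader might infer that every caregiver-related endpoint is biased the same way, or that placement simply scores as improvement. The documents do not support this. No section says so, and hypothesis 3 needs responsiveness to rise. If less contact lowers responsiveness, placement would count as worsening and a return home as improvement. The inference fits conflict and caregiver-rated aggression only.
- **Size.** A worked example with flat scores and placement after the first of 10 phase B measurements gives 9/10 = 90% non-overlap, above the cut. That result comes from leaving out all variation within phases; with variation, crossing the cut is uncommon unless the shift is large.

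**Conclusion.** The concern holds in a limited form. The criteria and phase definitions allow a case whose whole baseline is recorded away from home and whose return comes at the phase boundary or up to 3.7–5.7 weeks into phase B. For that case the change from baseline in conflict and caregiver-rated aggression cannot be assigned to FAST, and the likely error is to hide benefit. For responsiveness the direction is open. A placement during phase B or C is a separate route that could imitate benefit on conflict and caregiver-rated aggression.

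This assumes that these scores depend on contact, which the item wording makes plausible but the article does not measure. It also assumes that at least one enrolled family is affected. The article gives no such count, and criterion 8 speaks of an expected return, which may come early or not at all. The effect on the study as a whole therefore cannot be stated. For an affected case, a bias of roughly 0.4 to 1.6 SD follows from assumed shifts of 0.5 to 2 SD.

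**What to change.** - Add one item to every short questionnaire: the number of nights since the last questionnaire that the juvenile slept in the reporting caregiver's home. For families already enrolled, use dated residence from the case files where available.
- Mark each change of residence on the case's plot.
- Keep all measurements in the main analysis. Add a sensitivity analysis restricted to measurements with the same residence status, wherever each phase keeps enough of them; the Design section's own minimum of five is the natural threshold.
- Where residence changes at or near the A/B boundary, do not attribute that case's A–B change in conflict, responsiveness or caregiver-rated aggression to FAST.
- Report any out-of-home placement during phase B or C beside these endpoints, and do not read a later fall in conflict or caregiver-rated aggression as improvement.

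Two stronger remedies are not advised. Making at-home measurements the main analysis would leave away-baseline cases with no phase A data and, for placed juveniles, would condition on an event after treatment began. Requiring residence with the caregiver at entry would narrow the target group, against the article's stated interest in external validity.

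The cost is one item on a questionnaire of about 37, and a few cases that become inconclusive on the caregiver-related endpoints.
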